### Economic evaluation

The economic evaluation will be performed according to the intention-to-treat principle and from a societal perspective. Multiple imputation according to the MICE algorithm will be used to impute missing cost and effect data
[44].

All costs will be summed for each individual patient. Incremental cost-effectiveness ratios (ICERs) will be calculated by dividing the difference in total costs between the two groups by the difference in effects. Bias-corrected and accelerated bootstrapping with 5000 replications will be done to estimate the uncertainty surrounding the ICERs. Bootstrapped incremental cost-effect pairs will be plotted on cost-effectiveness planes to graphically illustrate the uncertainty around the cost-effectiveness ratios. A summary measure of the joint uncertainty of costs and effects will be presented using cost-effectiveness acceptability curves, which indicate the probability that the intervention is cost-effective in comparison with control at different ceiling ratios (i.e. the maximum amount of money society is willing to pay to gain one extra unit of effect). Sensitivity analysis on the most important cost drivers will be performed in order to assess the robustness of the results.

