***Primary outcomes***								
Functional status (ODI)	X			X	X	X	X	X
Pain intensity leg (NRS)	X	X		X	X	X	X	X
Pain intensity back (NRS)	X	X		X	X	X	X	X
Global perceived recovery (GPE)				X	X	X	X	X
General health status (SF-12)	X			X	X	X	X	X
Health related quality of life (EQ-5D)	X			X	X	X	X	X

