#### Primary outcome measures

The recommended core set of outcomes for low back pain research
[22] will be used, and all measures are self-reported.

Functional status will be assessed by the Oswestry Disability Index (ODI)
[23,24]. The ODI consists of 10 questions assessing aspects of daily living, each being scored on a six-point scale, ranging from 0–5. The total score comprises the 10 item-scores and ranges from 0 (no difficulty) to 50 (maximal difficulty).

Pain intensity will be measured for leg pain and low back pain on an 11-point numerical rating scale (0 = no pain to 10 = worst imaginable pain)
[25,26]. Average pain intensity over the preceding week will be measured, for leg pain and low back pain separately. At three days postoperative the pain at the time of measurement will be assessed, again for leg and back pain separately.

Global perceived recovery will be evaluated with the seven-point Global Perceived Effect scale (GPE), ranging from “completely recovered” to “worse than ever”
[22]. This will be dichotomised into success (completely and much recovered) and non-success (slightly recovered, no change, slightly worse, much worse and worse than ever).

The Medical Outcome Study Short Form 12 (SF-12) will be used to assess general health status
[27,28]. The 12 items cover the dimensions physical function and mental health. Sum-scales can be derived with scores ranging from 0–100 per dimension. Higher scores reflect better health.

The EuroQol (EQ-D5) will be administered to assess health related quality of life
[29,30]. This instrument evaluates 5 dimensions of quality of life on a three-point scale (no problems, moderate problems and severe problems). Utilities based on the EQ-5D will be estimated using the Dutch valuation tariff
[31].

Costs will be measured from a societal perspective using cost questionnaires. Only costs related to leg and back pain are considered and will include costs of continued rehabilitation, other health care costs, patient and family costs, and missed days of unpaid work. The cost questionnaires and the therapists’ registrations of sessions completed are also used to check compliance to the allocated treatment and possible cross-over, i.e. receiving exercise therapy in the control group either by means of direct access or referral.

A modified version of the Productivity and Disease Questionnaire (PRODISQ) will be used to evaluate absence from paid work

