### Sample size

Power calculations were based on a Cochrane review assessing the effectiveness of rehabilitation following lumbar disc surgery
[18] and were performed for the three main outcomes (for all: power 0.9; alpha 0.05). To detect a clinical relevant mean difference in a multi-level analysis between the continued rehabilitation group and the watchful waiting group of 8 points on the ODI (SD 15), a total of 165 patients is needed. To detect a difference of 2 points (SD 3) for pain (11-point NRS) a total of 105 patients is needed. For detecting a 20% difference on the dichotomised global perceived recovery (recovered vs not recovered) a total of 150 patients is needed. Anticipating 15% potential study withdrawal, a total of 200 patients will be recruited. Participants will be unequally distributed (109 intervention vs. 91 control) to allow for multilevel analysis, taking into account the multilevel structure of the data in the intervention group.

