### Data analysis

Baseline characteristics in both arms will be compared to check if randomisation has resulted in an equal distribution of the main outcome measures, prognostic factors and known confounding factors such as age, gender, living status and educational level.

The primary analysis will be an intention-to-treat analysis. All continuous responses will be analysed in a linear mixed model with responses at baseline and 3, 6, 9, 12 and 26 weeks. If necessary, missing items within a questionnaire will be imputed using multiple imputation techniques. In these analyses we will take into account the levels of neurosurgeon, primary care therapists, patient and time of measurement. The effect of interest for the present study will be the time by treatment interaction. Therefore, regression coefficients with 95% confidence intervals (CI) between baseline and follow up measurements will be calculated. If appropriate, analyses will be adjusted for patient characteristics that differ between the two groups. For the dichotomous outcomes we will use a generalised mixed model (logit link) with the same multilevel structure, and the effect of interest will be the difference between groups at each time point. Odds ratios with 95% CI between intervention and control groups will be calculated.

A per protocol analysis will be performed to estimate the extent to which protocol deviations may bias the results. A protocol deviation is defined as receiving one or more sessions of exercise therapy in the first six to eight weeks after surgery in the control group, or not receiving any sessions of exercise therapy in the first six to eight weeks postoperatively by participants in the intervention group.

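### The economic evaluation states no baseline adjustment, so as written an EQ-5D-based effect would leave unused the baseline utility that the trial collects

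*Protocol article*

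**What the plan says.** The Economic evaluation section lists its steps. Missing values: "Multiple imputation according to the MICE algorithm will be used to impute missing cost and effect data". Costs are summed per patient. The ICER comes from "dividing the difference in total costs between the two groups by the difference in effects". Uncertainty: "Bias-corrected and accelerated bootstrapping with 5000 replications will be done to estimate the uncertainty surrounding the ICERs". The bootstrapped pairs feed the cost-effectiveness plane and the acceptability curves. No step is a regression, no covariate is named, and the effect measures are not specified.

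Elsewhere in the article:

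- Table 1, under primary outcomes, has a row beginning "Health related quality of life (EQ-5D", marked at baseline and at 3, 6, 9, 12 and 26 weeks.
- Primary outcome measures: "Utilities based on the EQ-5D will be estimated using the Dutch valuation tariff". QALYs are not mentioned anywhere.
- Data analysis: "All continuous responses will be analysed in a linear mixed model with responses at baseline and 3, 6, 9, 12 and 26 weeks". It adds: "If appropriate, analyses will be adjusted for patient characteristics that differ between the two groups". It does not say whether either statement governs the economic evaluation.

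**The concern.** Preoperative utility usually predicts later utility. If the arms differ by chance at baseline, an unadjusted comparison of utility accumulated over follow-up carries part of that difference into the incremental effect, and from there into the ICER, the plane and the acceptability curve. Even with no imbalance, the comparison contains between-patient variation that a covariate already in the database could remove.

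It is easy to underrate this by looking only at baseline's direct weight in an area under the curve, which is small. Most of the influence runs through the correlation of baseline with every later visit.

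The Data analysis section does give baseline a role for continuous outcomes, so the economic section's silence leaves it open whether the same utilities would be handled in two different ways. Cost-effectiveness is in the trial's title and is one of its stated aims.

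**Working it through.** There is no figure in the plan to reproduce: it gives no utility SD, no correlation and no expected utility difference. The check shows what would be at stake if the effect were a 26-week area under the utility curve.

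**Inputs from the article:** EQ-5D visits at 0, 3, 6, 9, 12 and 26 weeks (Table 1); planned arms "109 intervention vs. 91 control" (Sample size).

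**Assumed:** trapezoid area under the curve; the same utility SD σ at all visits, 0.2 to 0.3; correlation 0.6 between follow-up visits; baseline-to-follow-up correlation ρ from 0.1 to 0.5; no clustering and complete data.

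**Step 1, weights.** The trapezoid rule gives 1.5, 3, 3, 3, 8.5 and 7 weeks, sum 26. Baseline's direct share is 1.5/26 = 5.8%. The follow-up weights sum to 24.5, and their squares sum to 3 × 9 + 72.25 + 49 = 148.25.

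**Step 2, slope of the area on baseline utility.** 1.5 + 24.5ρ weeks.

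**Step 3, variance of the area, in units of σ² and weeks².** The follow-up part is 0.6 × 24.5² + 0.4 × 148.25 = 360.15 + 59.3 = 419.45. In total: 2.25 + 2 × 1.5 × 24.5ρ + 419.45 = 421.70 + 73.5ρ.

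**Step 4, proportion of variance removed by adjustment.** R² = slope² / variance.

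**Step 5, chance imbalance.** SE of the baseline difference = σ√(1/109 + 1/91) = 0.142σ, which is 0.0284 at σ = 0.2 and 0.0426 at σ = 0.3. A 1.96-SE imbalance is 0.0557 or 0.0835.

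**Step 6, shift of the unadjusted difference.** Imbalance × slope / 52, in utility-years. Relative to the SE of the unadjusted difference it is 1.96 × R, whatever σ is.

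| ρ | slope (weeks) | variance | R² | shift, σ 0.2 | shift, σ 0.3 | shift in SEs |
|---|---|---|---|---|---|---|
| 0.1 | 3.95 | 429.05 | 3.6% | 0.004 | 0.006 | 0.37 |
| 0.2 | 6.40 | 436.40 | 9.4% | 0.007 | 0.010 | 0.60 |
| 0.3 | 8.85 | 443.75 | 17.7% | 0.009 | 0.014 | 0.82 |
| 0.5 | 13.75 | 458.45 | 41.2% | 0.015 | 0.022 | 1.26 |

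The direct part alone, through the 1.5-week weight, is only 0.0557 × 1.5/52 = 0.0016 to 0.0835 × 1.5/52 = 0.0024.

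In terms of standard errors at σ = 0.25, adjustment takes the SE of the difference from 0.0143 to 0.0136 at ρ = 0.2, and from 0.0146 to 0.0112 at ρ = 0.5.

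**The case against.** The strongest reply is that silence is being treated as a decision.

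- **The plan uses raw differences.** A reader might infer this, but the text does not say so. The words raw, crude and unadjusted do not appear, and the ICER sentence is the general definition, which fits adjusted differences equally well. What stands is that every estimation step is listed and none is an adjustment, so an analyst who follows the text gets unadjusted differences.
- **The ICER would be biased.** A reader might also infer this. Under randomisation the unadjusted difference is unbiased in expectation, and the planned bootstrap carries chance imbalance into the reported uncertainty. The 1.96-SE case is by construction a tail event. This objection stands in full and limits the point to precision and to accuracy given an observed imbalance.
- **The economic and clinical analyses contradict each other.** The documents do not show that either. The Data analysis section neither extends its baseline handling to the economic evaluation nor excludes it. This is an ambiguity.
- **The QALY is the reviewer's construction.** True: it is inferred from tariff-based utilities combined with an ICER, and every SD and correlation above is assumed. The documents cannot distinguish a 4% gain from a 41% gain.
- **A condensed article may leave the covariate model to a fuller plan.** This is fair. Absence alone would be no finding. The point rests on the procedure as written, set against a Data analysis section of the same article that does address baseline and covariates.

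**Conclusion.** The point holds as a modest improvement to the stated method. Followed as written, the Economic evaluation section gives between-group differences that make no use of baseline utility, and the adjustment rule under Data analysis is not said to apply there. The consequence is lost precision and exposure to chance imbalance; validity is not affected.

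For a utility-based 26-week effect, adjustment would reduce the variance of the difference by about 4% to 41% for a baseline-to-follow-up correlation of 0.1 to 0.5. For a correlation of 0.2 to 0.5 and a utility SD of 0.2 to 0.3, a 1.96-SE imbalance would move the difference by about 0.007 to 0.022. Both ranges depend on the assumed trapezoid area, equal SDs and follow-up correlation of 0.6. The article gives no expected effect or willingness-to-pay threshold against which to judge whether such a shift would change the conclusion.

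**What to change.** Add to the Economic evaluation section that the incremental effect is estimated by regression on arm with baseline EQ-5D utility as a prespecified covariate, fitted within each bootstrap replicate together with the cost comparison, so that the link between costs and effects is kept. For any other effect measure, use its own baseline where one exists; global perceived recovery has none in Table 1. State that the ICER, plane and acceptability curve all use these adjusted differences. Seemingly unrelated regression is one way to do this and is not required.

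Make the covariate unconditional, so that it does not depend on the baseline comparison of the arms. Also name the effect measures and say whether the Data analysis adjustment rule applies to the economic evaluation.

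The cost is a sentence or two and slightly more analysis work. No new data are needed.

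### A BCa bootstrap interval placed on the ICER itself under-covers when the effect is less than about two standard errors from zero; net-benefit intervals from the same bootstrap pairs avoid this

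*Protocol article*

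**What the plan says.** All of this stands in the Economic evaluation section of the protocol article.

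- The ICER is obtained by "dividing the difference in total costs between the two groups by the difference in effects".
- Its uncertainty is handled as follows: "Bias-corrected and accelerated bootstrapping with 5000 replications will be done to estimate the uncertainty surrounding the ICERs".
- Two displays follow. The first is the plane: "Bootstrapped incremental cost-effect pairs will be plotted on cost-effectiveness planes to graphically illustrate the uncertainty around the cost-effectiveness ratios". The second is the curve: "A summary measure of the joint uncertainty of costs and effects will be presented using cost-effectiveness acceptability curves".
- The ceiling ratio on the curve is described as "the maximum amount of money society is willing to pay to gain one extra unit of effect".

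The section gives no confidence level, cost standard deviation or expected cost difference. It also does not say which outcomes serve as the effects or how they are coded.

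**The concern.** The bias correction and the acceleration have one function: they move the percentile endpoints of the ordered bootstrap distribution of a scalar. They play no part in a scatter of cost-effect pairs or in an acceptability curve. A sentence that applies BCa to the uncertainty of the ICER therefore reads most naturally as an interval on the ratio.

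Such an interval needs replicates that can be ranked from low to high. ICER replicates can be ranked in that sense only while the effect difference keeps one sign. If it can cross zero, negative ratios mix better-and-cheaper with worse-and-dearer, positive ratios mix better-and-dearer with worse-and-cheaper, and the ratio jumps between plus and minus infinity at zero effect.

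Cost-effectiveness is in the title and the stated aim, so a poor interval on the headline economic figure matters. A small effect is a realistic possibility. The Discussion puts the main question as faster early recovery, the neurosurgeon may refer patients in either arm for treatment after the six-to-eight-week consultation, and cost questionnaires run to 26 weeks. The Sample size section has no power calculation for the EQ-5D.

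**Working it through.** The article states no ICER, interval or coverage, so there is no figure of its own to reproduce. The check has three steps.

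**1. Is the ratio ambiguous?** Illustrative values for (cost difference, effect difference):

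- (−500, +2): −500/2 = −250. (+500, −2): 500/(−2) = −250.
- (+500, +2): 500/2 = +250. (−500, −2): −500/(−2) = +250.

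Opposite quadrants cannot be told apart from the ratio alone.

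**2. How often do replicates cross zero effect?** Inputs from the Sample size section: ODI SD 15, target difference 8, 109 and 91 patients, 15% withdrawal.

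- Patients left: 109 × 0.85 ≈ 93 and 91 × 0.85 ≈ 77, total 170.
- SE = 15 × √(1/93 + 1/77) = 2.31 points. Clustering and baseline adjustment are ignored.
- 1.96 × 2.31 = 4.5 points. Below an observed gain of about 4.5, more than 2.5% of replicates have zero or negative effect.
- In SE units: 2/2.31 = 0.87, 4/2.31 = 1.73, 8/2.31 = 3.46.

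In simulation, the share of trials above that 2.5% mark was 87–88% at a true gain of 2 points, 58% at 4 and 6–8% at 8.

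**3. What does the BCa interval on the ratio cover?** Costs are assumed throughout. Coverage of the true ICER by a nominal 95% BCa interval, 93 vs 77 patients, SD 15:

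| Run | Gain 2 | Gain 4 | Gain 8 |
|---|---|---|---|
| A: gamma costs (mean 4000, SD 5000 euros), extra cost 0 or 500, independent of effects; 300 trials, 2000 replicates | 78–81% | 89–91% | 93–95% |
| B: separate run, gamma costs | 78–82% | about 92% | 92–95% |
| C: check run, settings of A with 1000 trials | 75–79% | 89–93% | 94–95% |

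The Monte Carlo SE is about 1 to 2.5 percentage points in A and about 1 point in C.

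Run D worked in SE units with different costs: SD 3000, normal or lognormal, correlation with effect 0 or −0.3, cost difference −1 to +2 SE, 1000 trials, 5000 replicates.

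| True effect | BCa coverage of the ICER |
|---|---|
| 0.1–0.5 SE | 41–74% |
| 1 SE | 77–83% |
| 1.5 SE | 84–89% |
| 2 SE | 91–94% |
| 3.3–3.46 SE | 94–96% |

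At 1 SE about 24% of bootstrap pairs lay on the wrong side of the effect axis. The runs agree despite different cost assumptions, because the ratio of the true effect to its SE drives the result.

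**Mechanism.** The bias correction depends on the share of replicates below the estimate. Replicates that change sign distort that share, and BCa treats the distortion as bias. In run C the mean absolute correction was about 0.46–0.50 at a 2-point gain and 0.03 at 8 points.

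**Alternatives.** Incremental net benefit is ceiling ratio × effect difference − cost difference. It is linear in both differences and has no singularity. Percentile intervals for it covered 92–96% in D; BCa intervals covered 94–95% in B and 92–96% in C. Plain percentile intervals on the ratio are not a safe substitute. In D they covered 95% or more at 0.5 to 2 SE, but only 56–73% at 0.1 SE when the cost difference was not zero, and their ranking has the same quadrant problem.

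**The case against.** The strongest reply is that no ICER interval is promised. The Data analysis section names 95% confidence intervals where it wants them; the Economic evaluation section names none, and its next sentences show the uncertainty through planes and acceptability curves, which do separate the quadrants. The low coverage also requires true gains of 2 or 4 points, below the 8 points the plan calls clinically relevant, and rests on assumed costs. At the planned pain effect, 2/(3 × √(1/93 + 1/77)) = 4.3 SE, the interval should behave at least as well.

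Much of this stands, and it limits the harm. It does not remove the point. BCa is named, it is attached to the ICER, and it produces nothing except interval endpoints. Valid displays beside an invalid interval do not make the interval valid, and a method should hold up when the effect turns out small.

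Two stronger readings are tempting, and the document supports neither.

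- A reader might infer that ODI and pain enter with the sign reversed, since the ODI "ranges from 0 (no difficulty) to 50 (maximal difficulty" and pain runs "0 = no pain to 10 = worst imaginable pain". Those are raw questionnaire ranges. The economic section does not name its effects or their coding, and its wording of one unit gained suggests an improvement scale. An article may leave the coding to the full plan.
- A reader might infer that the ICER itself is wrong. It is a correct ratio that has to be read with its quadrant, and the plan plots the quadrants.

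**Conclusion.** The point holds in a limited form. Read as written, the plan puts a BCa interval on a ratio whose replicates cannot be ranked once the effect difference crosses zero. Against a nominal 95%, coverage is about 78–82% at a true 2-point ODI gain (a check run gave slightly less) and about 89–92% at 4 points. It worsens nearer to zero and is close to nominal at the planned 8 points.

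These figures rest on the plan's SD and sample size, on independent patients, on a 95% level the section does not state, and on assumed cost distributions. The last matters little beside the ratio of effect to SE. The point estimate, the planes, the acceptability curves and the effectiveness analysis are untouched. The change is worth making because the method is stated and the remedy is cheap.

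**What to change.** In the Economic evaluation section, replace the sentence on BCa bootstrapping of the ICER with wording such as: 5000 bootstrap pairs of cost and effect differences will be drawn; the ICER will be reported as a point estimate with the percentage of pairs in each quadrant of the plane; BCa 95% confidence intervals will be given for the cost difference, the effect difference and the incremental net benefit over the range of ceiling ratios. Keep the planes and the acceptability curves as planned.

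The cost is one or two sentences of analysis text. The same pairs are reused, with no additional patients, data or resampling. The small downside is that readers who expect a single interval next to the ICER will not find one.

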## Discussion

A systematic review that summarised results of several randomised controlled trials yielded moderate to low quality evidence for effectiveness of postoperative exercise programmes starting 4–6 weeks after first time lumbar disc surgery
[18]. Exercise programmes seem to be more beneficial than no treatment, and high intensity exercises may be more effective than low intensity exercises. Little is known about the effectiveness of immediate postoperative interventions in these patients
[18]. Besides, knowledge about cost-effectiveness of postoperative management is scarce
[19]. Therefore, the REALISE trial aims to evaluate the effectiveness of an exercise therapy intervention starting in the first postoperative week, compared to a watchful waiting policy during the first six to eight weeks after surgery. To that end we mainly focus on the question whether exercise treatment leads to a faster recovery as compared to watchful waiting during this immediate post operative period. Furthermore, cost-effectiveness will be assessed by means of an economic evaluation. Treatment in the intervention group is based on a protocol that allows therapists to provide a tailored intervention. Also, both physiotherapists and exercise therapist will deliver the treatment, as this reflects current practice in the Netherlands. This will result in a variation across treatments and will improve generalisability of the findings. The results of this trial may lead to a more consistent postoperative strategy for patients who underwent surgery for lumbar disc herniation.
